### 2.4. Outcomes

To evaluate the effectiveness of the mobile app, data will be collected five times from all participants: At enrolment, before discharge from hospital, 1 month, 4 months, and 6 months postpartum. The first two data collections will be conducted by face–to–face interviews and the three follow up surveys will be performed through telephone conversations. Definitions of breastfeeding from the World Health Organization (2008) will be adopted for the evaluation of the outcomes [5], based on both recall of the previous day and recall since birth methods [5,122,123]:early initiation of breastfeeding: Proportion of infants at the first month of age who were put to the breast within one hour of birth;exclusive breastfeeding: Proportion of infants at 1, 4, 6 months of age who were fed by breast milk only during the previous day, and from birth;predominant breastfeeding: Proportion of infants at 1, 4, 6 months of age who received breast milk as the predominant source of nourishment during the previous day, and from birth;any breastfeeding: Proportion of infants at 1, 4, 6 months of age who were ever breastfed;duration of exclusive breastfeeding: The age in weeks when infants received only breast milk from birth;introduction of complementary and solid foods: Proportion of infants at 1, 4, 6 months of age who received solid, semi-solid, or soft foods.

Confounding variables will be identified from an extensive literature review, including: (1) Socio-demographic characteristics such as age, marital status, education level, occupation, household income, parity, smartphone usage experience; (2) obstetric and birth outcomes: Complications during and after pregnancy, mode of delivery, length of hospital stay, infant gender, birth weight and length; (3) breastfeeding attitude and intention on breastfeeding. Such information will be collected prospectively from the baseline and follow up surveys.

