The East Asia and the Pacific Regions have the lowest rates of early initiation of breastfeeding (36%) and reported period prevalence (0–6 months) of exclusive breastfeeding (27%) [42]. In 2019 UNICEF reported exclusive breastfeeding rates (<6 months) of 24% in Vietnam, early initiation of breastfeeding 26%, continued breastfeeding (12–23 months) 43%, including 55% in the poorest quintile and 29% in the richest quintile [43]. The early initiation rate has declined from 74% in a 2004 study to the present low level of 26% [44]. In this study, mothers who delivered at home had an early initiation rate of only 24%. By week 16 the exclusive breast feeding had dropped to 44% and no-one was exclusively breastfeeding at 6 months [45]. In 2016, only 40% of infants had “early initiation” of breastfeeding, while 17% of infants aged 0–5 months received only breast milk during the previous day (i.e., period prevalence 0–6 months) [46]. The exclusive breastfeeding rate at 6 months was less than 1% [47]. In a large cohort study (*n* = 1709), the prevalence of prelacteal feeding was high (56.5%) and formula feeding was common (79.5%) before hospital discharge. This increased the risks of hospitalisation by 2 months for prelacteal feeds and infant formula use [48]. 

In Vietnam, it has been projected that improved breastfeeding rates would prevent between 2000 and 8000 infant deaths annually and around 500 mothers dying from breast cancer [1,49]. Although increases in breastfeeding rates have been observed in some developing countries [50], the breastfeeding prevalence continues to decline in Vietnam, particularly in urban areas [46,51] and following caesarean delivery [46,47]. However, the surveys reported used different methodologies and the review by Cai used 24 h recent feeding in a cross-sectional survey and the results completely depend on the age of the infants being surveyed [50].

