### 2.5. Sample Size

The Clinical Calculators ClinCalc program is used for sample size estimation [124] following the formula for statistical superiority design with a dichotomous variable [125]. Among the above outcomes, the period prevalence of exclusive breastfeeding at 6 months is selected for sample size calculation: 12.6% in Hanoi in 2014 [109]. Assuming the prevalence to increase to 20% in the intervention group, the required sample size is 780 (390 per group) with 80% power at 5% level of significance. 

After accounting for a potential 15% loss of follow up from pregnancy to delivery and further 1–2% at each time point of the follow-up period, a final sample size of 1000 women will be recruited at baseline. We anticipate a high loss of follow up the rate at the initial stage due to mothers changing their minds and delivery at a different hospital and the possibility of incurring medical conditions or pregnancy complications that prevent breastfeeding. This sample size of 1000 allows about 20% loss of follow up for evaluation at 6 months [126]. Participants will be consecutively recruited from the two hospitals until reaching the desired sampling size.

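### The outcome 'any breastfeeding' at 1, 4 and 6 months is worded as a cumulative 'ever' status, so it repeats initiation and cannot show whether breastfeeding continued

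*Protocol article*

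**What the plan says.** Section 2.4 lists the outcomes under a general statement that they are "based on both recall of the previous day and recall since birth methods". The items that matter here are:

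- Exclusive breastfeeding at 1, 4 and 6 months: infants "who were fed by breast milk only during the previous day, and from birth".
- Predominant breastfeeding at the same ages: infants "who received breast milk as the predominant source of nourishment during the previous day, and from birth".
- The item in question: "any breastfeeding: Proportion of infants at 1, 4, 6 months of age who were ever breastfed".

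The list also contains early initiation, duration of exclusive breastfeeding, and introduction of complementary and solid foods. The only duration outcome is for exclusive breastfeeding.

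Section 1.1 reports continuation as an indicator in its own right, separate from early initiation: "continued breastfeeding (12–23 months) 43" per cent for Vietnam.

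Section 2.5 rests the sample size on a different outcome: "the period prevalence of exclusive breastfeeding at 6 months is selected for sample size calculation: 12.6% in Hanoi in 2014".

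**The concern.** The label, and the choice of three follow-up ages, promise a measure of how many infants still receive breast milk as they grow older. The definition delivers something else. A status that can never revert cannot record stopping, so a figure headed any breastfeeding at 6 months would really be a figure for having started.

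Two things are at stake. First, a reader of the results would naturally take the 6-month proportion as continuation and would be misled. Second, if the app helps mothers keep breastfeeding alongside other feeds, this outcome cannot register it. Section 2.3 says the messages address breastfeeding difficulties and the perception of insufficient milk, both of which plausibly bear on continuation. Partial breastfeeding is unlikely to be rare in this setting: Section 1.1 cites a large cohort in which 79.5% of infants had formula before hospital discharge.

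**Working it through.** **1. Logic of the definition.** Let E(t) = 1 if an infant has been breastfed at any time up to age t. Then E(1) ≤ E(4) ≤ E(6) for every infant, because the event cannot be undone. In a fixed cohort the proportion cannot fall between visits. It can rise only if breastfeeding begins after the first month. An observed fall could come only from attrition, a changed denominator or inconsistent recall, and none of these is stopping. This step needs no assumed rate.

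**2. Does another listed outcome fill the gap?** Take two infants given formula from the same early age. Infant A still receives some breast milk at 6 months, but formula is the main feed. Infant B was weaned in the first week.

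| Outcome in Section 2.4 | Infant A | Infant B |
|---|---|---|
| Early initiation | same | same |
| Exclusive at 6 months | no | no |
| Predominant at 6 months | no | no |
| Any breastfeeding (as worded) at 6 months | yes | yes |
| Duration of exclusive breastfeeding | same | same |
| Complementary foods | can be the same | can be the same |

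The two records can be identical on every listed outcome. Continued partial breastfeeding is not captured.

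**3. Size of the gap, as an illustration.** The documents give neither an ever-breastfed rate nor a 6-month continuation rate for this population, so these inputs are assumptions. Current any breastfeeding = proportion starting × proportion of starters still breastfeeding.

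- With 95% starting and 90%, 80% and 70% of starters continuing at 1, 4 and 6 months:
  - as worded: 95%, 95%, 95%;
  - current status: 0.95 × 0.90 = 85.5%; 0.95 × 0.80 = 76.0%; 0.95 × 0.70 = 66.5%.
- Over a range of 90% to 98% starting and 70% to 80% continuing at 6 months:
  - as worded: 90% to 98%;
  - current status: 0.90 × 0.70 = 63% to 0.98 × 0.80 = 78%.
- If both arms start at 95% and 6-month continuation among starters is 70% in one arm and 80% in the other:
  - as worded, the expected difference is 0;
  - current status differs by 76.0% − 66.5% = 9.5 points.

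**4. Is the sample size touched?** Inputs from Section 2.5: 12.6% against 20%, 80% power, 5% level (taken as two-sided), with the 1:1 allocation of Section 2.1. With pooled variance, mean proportion (0.126 + 0.20)/2 = 0.163:

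n = [1.960 × √(2 × 0.163 × 0.837) + 0.842 × √(0.126 × 0.874 + 0.20 × 0.80)]² / 0.074²

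= [1.960 × 0.5224 + 0.842 × 0.5197]² / 0.005476 ≈ 2.135 / 0.005476 ≈ 390 per group, 780 in all.

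This matches the plan: "the required sample size is 780 (390 per group) with 80% power at 5% level of significance". Any breastfeeding does not enter the calculation.

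**The case against.** The strongest defence is that the line is only loosely condensed. The lead-in applies to the whole list and names previous-day recall. With the label and the three ages, it suggests that current feeding was meant, and that ever breastfed is merely the since-birth version of the item. That is plausible as to intent, and it is why this reads better as an internal inconsistency than as a deliberate decision to measure initiation alone. It does not cure the text. The exclusive and predominant items write out both windows; this one gives only the cumulative status, and an analyst following it would derive the wrong variable.

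The second defence is that the outcome is peripheral, and this stands. The objective (Section 1.3), the design statement (Section 2.1), the sample size (Section 2.5), the named analyses (Section 3.5) and the hypothesis (Strengths and Limitations) all concern exclusive breastfeeding. None names continuation of any breastfeeding as a target.

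Three stronger readings are tempting and are not supported:

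- A reader might infer that the trial's main conclusion is compromised. It is not, for the reason just given.
- A reader might infer that this is the only item in the list without a time window. The complementary-food item also states none. The contrast holds only against the exclusive and predominant breastfeeding items.
- A reader might infer that the outcome is bound to sit near 100% in both arms with very low power. The documents give no ever-breastfed rate, so any such power figure would rest wholly on assumed rates, and the trial was not sized for this outcome anyway. The argument does not need it.

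**Conclusion.** The point holds as a defect in one outcome definition. As written, any breastfeeding at 1, 4 and 6 months essentially repeats initiation three times, cannot show stopping, and leaves continued partial breastfeeding unmeasured by any listed outcome. That conclusion follows from the wording alone. Only the illustrative gap (90% to 98% as worded against 63% to 78% current at 6 months) rests on assumed rates.

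The severity is moderate to minor. One outcome outside the sample-size calculation is affected, and the exclusive breastfeeding analyses and the 390 per group stand. If previous-day feeding is recorded in enough detail, the intended variable can still be derived before analysis, so nothing need be lost.

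**What to change.** In Section 2.4, define any breastfeeding as the proportion of infants at 1, 4 and 6 months who received any breast milk during the previous day, whatever else they were fed. Report ever breastfed once, from the discharge or 1-month interview, as a measure of initiation.

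The cost is one line in the outcome list and the matching derivation. The previous-day recall planned for exclusive and predominant breastfeeding probably supplies the data. Because the questionnaire is not shown, the trial team should confirm that it records any breast milk in the previous day separately from other feeds. The change should be dated before outcome data are examined by group, so that it is not read as a post-hoc redefinition. No sample-size figure changes.

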### 2.5. Sample Size

The Clinical Calculators ClinCalc program is used for sample size estimation [124] following the formula for statistical superiority design with a dichotomous variable [125]. Among the above outcomes, the period prevalence of exclusive breastfeeding at 6 months is selected for sample size calculation: 12.6% in Hanoi in 2014 [109]. Assuming the prevalence to increase to 20% in the intervention group, the required sample size is 780 (390 per group) with 80% power at 5% level of significance. 

After accounting for a potential 15% loss of follow up from pregnancy to delivery and further 1–2% at each time point of the follow-up period, a final sample size of 1000 women will be recruited at baseline. We anticipate a high loss of follow up the rate at the initial stage due to mothers changing their minds and delivery at a different hospital and the possibility of incurring medical conditions or pregnancy complications that prevent breastfeeding. This sample size of 1000 allows about 20% loss of follow up for evaluation at 6 months [126]. Participants will be consecutively recruited from the two hospitals until reaching the desired sampling size.

## 3. Randomisation and Masking

### 3.1. Randomisation Procedure

Permuted-block randomisation method with block sizes of 2, 4, and 6 will be used with stratification based on age (<30 vs. ≥30 years), education level (<tertiary education vs. ≥tertiary education) and parity (<2 vs. ≥2 children) to achieve the balance of the number of participants allocated to each treatment group [127,128]. These three factors were selected because they are important prognostic factors of breastfeeding outcomes [129,130].

### 3.2. Sequence Generation

The randomisation list will be generated by an independent statistician using the Stata “ralloc” procedure with the randomisation-stratified scheme described above (StataCorp, College Station, TX, USA). The randomisation list with a 1:1 allocation ratio will be configured into the Research Electronic Data Capture (REDCap) software hosted at Curtin University in Perth, Australia. REDCap is a secure, web-based software platform designed to support data capture for research studies, providing (1) an intuitive interface for validated data capture; (2) audit trails for tracking data manipulation and export procedures; (3) automated export procedures for seamless data downloads to common statistical packages; and (4) procedures for data integration and interoperability with external sources [131,132].

### 3.3. Allocation Concealment Mechanism

A statistician of the research team will undertake randomisation using REDCap following the completion of baseline interview for each participant, and group allocation will be conducted via a website (https://vbf.geomatics.vn/) to activate the participant’s mobile app based on a unique identifier. Participants, research assistants and data analysts will be kept blinded to group assignments.

### 3.4. Implementation

Research assistants (data enumerators) from the Hanoi University of Public Health will recruit and enrol pregnant women who attend antenatal care clinics. They will invite eligible women to participate in the study, collect consent forms, help with downloading, installation, and provide guidance on using the mobile app. They will also interview consenting participants at the baseline survey. After the mobile app is activated, notifications and library information will be automatically sent to participants according to their assigned group (intervention or control). After delivery, the app will be updated to provide appropriate messages. Research assistants will follow up mothers by telephone interview at 1, 4, and 6 months postpartum.

### 3.5. Analytical Methods 

Data will be collected and managed using REDCap [131] and exported to Statistical Package for the Social Sciences, SPSS. Survival analysis will be used to compare the exclusive breastfeeding duration between the intervention and control groups. The Kaplan–Meier curves will be used for estimating the median exclusive breastfeeding times, and the log-rank test will be used to assess the differences between groups. Multivariable logistic regression and repeated measures mixed modelling will be applied to determine the effect of the intervention on exclusive breastfeeding prevalence at different time-points, accounting for delivery method, and other confounding factors. Intention-to-treat analysis will be performed in the presence of missing data to accommodate the expected attrition and withdrawal of participants from the study. All statistical analyses will be performed in SPSS (IBM Corp. Released 2017. IBM SPSS Statistics for Windows, Version 25.0. Armonk, NY, USA: IBM Corp).

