### 2.2. Participants

The study is conducted in Hanoi City, Vietnam. Hanoi is the capital of Vietnam and the second-largest city by population (7.4 million inhabitants in 2017) [108]. Breastfeeding rate within one hour of birth was low at 45.2%, while exclusive breastfeeding rate within the three first days was only 25.8%. The rate of predominant breastfeeding until the first 6 months was 12.6%, lower than the national level [109]. In Hanoi, the internet was the second most popular source of information mothers looked for and it had increased exponentially from 21.8% to 41.8% within the period 2012–2014 [109]. This presents an opportunity to implement an intervention using a mobile application, especially because of the high smartphone usage in the major cities of Vietnam (84%), including Hanoi [110].

We will recruit mothers who intend to deliver in either at Dong Anh general district hospital or Hanoi Gynaecology and Obstetrics hospital. The Dong Anh general district hospital is a typical hospital in a suburban district of Hanoi. The hospital had 6000 deliveries per year, 41% of which were caesarean sections. The Hanoi Obstetrics and Gynaecology hospital serves its nearby residents in the city centre, and assists an average of approximately 44,000 deliveries per year, with around 53% undergoing caesarean sections.

Mothers can be included if meeting the following criteria:attending antenatal clinics at 24–36 weeks of gestation;own a smartphone with at least:
iOS version 11 (announced from 2017, support for iPhones from 2015)Android 5 (released from 2014);carrying a singleton foetus.

Mothers will be excluded if they meet any of the following criteria:being referred from other hospitals for high-risk pregnancy treatments;receiving advice from doctors against breastfeeding because of her health condition (e.g., positive T-cell lymphotropic virus, untreated brucellosis, varicella, H1N1 influenza) [111];where an infant is born with a birth weight of less than 2500, or is admitted to neonatal intensive care unit, the mother will continue receiving information from the app, but will be excluded from the analysis;if the infant has any of the infections or metabolic conditions as advised by the WHO or the Ministry of Health, where breastfeeding is contraindicated [11,112].

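### Kaplan-Meier medians are likely to be uninformative for exclusive breastfeeding duration: on the Hanoi figure the control median falls in week 0, and the intervention median probably does too

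*Protocol article*

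**What the plan says.** Section 3.5 (Analytical Methods) compares duration between the arms by survival analysis, with Kaplan-Meier curves used for "estimating the median exclusive breastfeeding times, and the log-rank test will be used to assess the differences between groups". The median is the only summary of duration that the article names. Section 2.4 (Outcomes) defines duration as an age in weeks during which the infant had only breast milk since birth. The Strengths and Limitations section makes longer duration part of the trial hypothesis, beside higher rates.

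The article gives several figures on how early exclusive breastfeeding ends:

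- Section 2.2, for Hanoi: "exclusive breastfeeding rate within the three first days was only 25.8" per cent.
- Section 1.1, for a cohort of 1709: "the prevalence of prelacteal feeding was high (56.5%) and formula feeding was common (79.5%) before hospital discharge".
- Section 1.1, for an earlier study: "By week 16 the exclusive breast feeding had dropped to 44% and no-one was exclusively breastfeeding at 6 months".

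The planned effect is set in section 2.5 (Sample Size), where "the period prevalence of exclusive breastfeeding at 6 months is selected for sample size calculation: 12.6% in Hanoi in 2014", with 20% assumed in the intervention group.

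**The concern.** A median describes a time-to-event curve well when the curve crosses one half at an informative time. Here most control infants would have had their event within days of birth, before the first follow-up and within the first unit of the time scale. The median then records only that more than half of the infants stopped in the first days. It is blind to everything the app might do among those who continue, and to any early gain that does not lift the arm above 50%.

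At stake is the effect size for duration. The plan names a test and a median. If both medians are in week 0, a significant log-rank result would stand beside a reported difference of zero weeks, and readers would have no usable estimate of how much exclusive breastfeeding time was gained.

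**Working it through.** **1. The plan's own figure.** For 12.6% against 20%, two-sided 5%, 80% power and pooled variance without continuity correction, the required number is 390 per group, 780 in total. This matches section 2.5, so the design effect is used as stated.

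**2. Control arm.** Let S(t) be the proportion still exclusive from birth at time t. Section 2.2 gives S(3 days) = 0.258. Since 0.258 < 0.5, the median is below 3 days, which is week 0. If the hazard is constant over those days, the median is 3 × ln(0.5)/ln(0.258) = 1.5 days. The section 1.1 cohort agrees: 79.5% formula use before discharge leaves at most 100 − 79.5 = 20.5% exclusive.

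**3. Intervention arm.** No early rate is given, so this step is an assumption. The 6-month effect is carried back to day 3 in four ways:

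| Effect held constant | Size at 6 months | S(3 days), intervention |
|---|---|---|
| Risk difference | 0.20 − 0.126 = 0.074 | 0.258 + 0.074 = 33.2% |
| Hazard ratio | ln(0.20)/ln(0.126) = 0.777 | 0.258^0.777 = 34.9% |
| Odds ratio | (0.20/0.80)/(0.126/0.874) = 1.734 | odds 0.258/0.742 × 1.734 = 0.603, so 37.6% |
| Risk ratio | 0.20/0.126 = 1.587 | 0.258 × 1.587 = 41.0% |

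All four are below 50%, so this median is also below 3 days (about 2.0 days under proportional hazards).

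**4. What would move the intervention median past day 3.** It needs S(3 days) ≥ 0.50, a gain of 24.2 points or a risk ratio of 0.50/0.258 = 1.94. The same effect held to 6 months implies:

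- risk ratio 1.94: 0.126 × 1.94 = 24.4%
- odds ratio 1/(0.258/0.742) = 2.88: odds 0.126/0.874 × 2.88 = 0.415, so 29.3%
- hazard ratio ln(0.5)/ln(0.258) = 0.512: 0.126^0.512 = 34.7%
- risk difference 0.242: 0.126 + 0.242 = 36.8%

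Each exceeds the 20% on which the trial is sized.

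**5. What a restricted mean would show.** As an illustration, take an exponential decline from the day-3 value a to the 6-month value b over 26 weeks, ignoring the first three days. The area is 26 × (a − b)/ln(a/b).

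- Control: 26 × (0.258 − 0.126)/ln(0.258/0.126) = 3.432/0.717 = 4.8 weeks.
- Intervention, proportional hazards: 26 × (0.349 − 0.200)/ln(0.349/0.200) = 3.875/0.557 = 7.0 weeks.

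The difference is about 2.2 weeks (2.0 to 2.8 across the four rows in step 3), against 0 weeks for the medians.

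**6. The log-rank test.** Expected events are 390 × 0.874 + 390 × 0.80 = 653. At hazard ratio 0.777 the Schoenfeld formula gives 89.7% power. A simulation of 390 per arm (3000 runs, no censoring before 26 weeks) gave 90% with the first three days resolved, and about 85% when the early drop is one tie on a weekly scale. If the effect begins only after day 3, simulated power was about 40% and 67% respectively. The test does not use the median, but the way first-week endings are recorded affects it.

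**The case against.** The strongest case is that the median is only descriptive. The between-arm comparison of duration rests on the log-rank test, the trial is sized on 6-month prevalence, and exclusive breastfeeding from birth at 1, 4 and 6 months is already an outcome. All of this stands, and it limits the consequence to the duration summary.

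Second, the intervention median is not fixed by anything in the article. That also stands. Section 1.3 cites an intervention in Vietnam with 16.0% against 3.9% exclusive breastfeeding, so a near doubling is not out of the question. It would, however, exceed the effect assumed in section 2.5.

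Third, other figures in section 1.1 point to longer medians. In the cohort, 100 − 56.5 = 43.5% had no prelacteal feed, and from that start the same four calculations give 51-69% in the intervention arm. But 43.5% is not an exclusive breastfeeding rate: formula use in the same cohort caps exclusivity before discharge at 20.5%. The 44% at week 16 comes from a study in which nobody was exclusive at 6 months, which does not fit the 12.6% used for the sample size.

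A reader might go further and infer that the log-rank test is unstratified and ignores the randomisation factors and hospital. The text does not say so. Age, education and parity are among the listed confounders in section 2.4, and Strengths and Limitations leaves covariate adjustment to an analysis plan that is not shown. Hospital is named in no analysis, but leaving it out does not bias an individually randomised comparison.

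**Conclusion.** The point holds for the median. On the article's Hanoi figure, the control median of exclusive breastfeeding duration falls in week 0. The intervention median probably does too, with 33-41% still exclusive at day 3 if the 6-month target effect applies from the start. The medians would then show no difference although the app met its target, while restricted mean time in the illustration differs by about 2 to 3 weeks.

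Three assumptions carry this. The 25.8% must apply to trial controls; excluding infants under 2500 g or admitted to intensive care could raise it somewhat. The effect at day 3 must resemble that at 6 months. And 12.6% must be an exclusive rate, as section 2.5 has it, although section 2.2 calls the same figure predominant breastfeeding.

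It would be too strong to say that the article's own figures put both medians in week 0, since it gives no early intervention rate. Nor is the duration test invalid: the log-rank comparison does not depend on the median, and the prevalence analyses are untouched. This is a worthwhile improvement to a stated method, not a threat to the trial's main conclusion.

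**What to change.** In place of the medians, or next to them, report:

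- the difference in restricted mean exclusive breastfeeding time to 26 weeks, with a confidence interval;
- Kaplan-Meier percentages at 1, 4 and 6 months by arm. These largely coincide with the from-birth prevalence already planned, so they add little work.

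State that infants with zero duration stay in the risk set, and record cessation in the first week in days. Fix the handling of first-week ties in advance, because it affects the power of the log-rank test.

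The cost is a short script or macro beside SPSS for the restricted mean, and a small change to the discharge and 1-month questions. It is therefore not purely a change of wording.

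An optional minor addition is to state that the log-rank test is stratified by the age, education and parity groups used in randomisation. The expected gain is at most a few points of power: about 0.5 to 3 in a simulated binary analogue with assumed stratum effects.
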